## Abstract

**Introduction:**

Individuals with spinal cord injury (SCI) face heightened cardiovascular disease (CVD) risks. While general exercise guidelines are promoted for SCI individuals, when and how to incorporate exercise during the subacute phase post-SCI remains unclear. Consequently, early aerobic exercise to reduce CVD risks is not standard practice in subacute SCI care, potentially missing an opportunity for optimal cardiovascular rehabilitation, especially given observed reductions in cardiac structure and function within the first year post-SCI. Addressing this gap could improve long-term cardiovascular health and health-related quality of life (HRQOL) for individuals with SCI. Early intervention might prevent worsening cardiovascular function and establish beneficial exercise habits. However, few studies have evaluated the effectiveness of early exercise interventions in this population. This study aims to provide insight into the impact of moderate-intensity arm-crank exercise training (ACET) on cardiometabolic, HRQOL, functional and fitness parameters in individuals with subacute (<12 months postinjury) SCI.

**Methods and analysis:**

We will conduct a single-centre, two-group, single-blind randomised controlled trial with 42 participants who have sustained a cervical or thoracic SCI within the past year. The non-intervention group will receive hospital standard of care (control group) while the intervention group will receive hospital standard of care plus moderate-intensity ACET for 10 weeks in line with the SCI-specific exercise guidelines to improve cardiometabolic health. The primary outcome measure will be central arterial stiffness (carotid-to-femoral pulse wave velocity). Secondary outcomes include assessments of (1) blood biomarkers linked to CVD, (2) cardiac structure and function, (3) extracranial vasculature, (4) HRQOL, (5) cognitive function, (6) physical activity level, (7) cardiorespiratory fitness, (8) motor function and (9) feasibility outcomes. Assessments will occur at baseline (rehabilitation centre admission, −2 weeks), preintervention (0 weeks), postintervention (10 weeks) and follow-up (6 months after postintervention), for HRQOL outcomes only.

**Ethics and dissemination:**

Ethical approval was obtained from the Wales Research Ethics Committee (HREC 22/WA/0329). Outcome data will be presented at international conferences, patient advocacy groups, health professional networks and community health events. Findings will be published in peer-reviewed journals and widely disseminated through strategic channels to reach researchers, healthcare providers, patients and the public.

**Trial registration number:**

ISRCTN99941302.

Strengths and limitations of this studyA longitudinal study design will allow us to look at changes in cardiovascular risk factors over time in the standard of care group (at a National Health Service (NHS) Spinal cord injury (SCI) rehabilitation centre) compared with the intervention group, who perform the population-specific exercise guidelines to try and mitigate declining cardiovascular health, thereby filling an important gap in understanding the benefits of early exercise interventions for people with SCI.The data collection in this trial encompasses measures of both traditional and non-traditional prognostic risk factors for cardiovascular disease.The outcome measures have demonstrated validity and reliability, specifically in individuals with SCI.Study recruitment and procedures will occur in one SCI rehabilitation centre to control for variation in the standard care provided to both groups; therefore, the findings may not be generalisable to all in-patient care settings in the UK.

## Background

 Spinal cord injury (SCI) is a life-altering event that can result in disruption to normal sensory, motor and/or autonomic functions,^1 2^ leading to a wide range of physiological and psychological consequences. Living with SCI can place a significant economic burden on patients, their families and the healthcare system, as it requires substantial healthcare resources.^3^ Recent improvements in technology, medical and rehabilitative care have led to individuals with SCI living significantly longer postinjury,^4^ with the odds of death during the first year postinjury being reduced by 67% for individuals injured between 1993 and 1998 relative to individuals injured between 1973 and 1977.^5^ Nevertheless, individuals with SCI are experiencing an accelerated trajectory of diseases and disorders that resemble those experienced with ageing alone.^6^

The dysregulation of the autonomic nervous system following SCI can play a role in the development of secondary conditions,^7^ contributing to the premature mortality in the SCI population being up to three times higher compared with the non-injured population.^8^ The primary cause for morbidity and mortality in individuals with SCI is the development of cardiovascular disease (CVD),^9^ which occurs earlier and affects over 60% of the SCI population.^10^ Early arterial remodelling represents a myriad of structural and functional changes of the vascular wall in response to sustaining an SCI, which has also been associated with haemodynamic changes and increased cardiovascular morbidity and mortality.^11^ Carotid-to-femoral pulse wave velocity (cfPWV), which is a measure of central artery stiffness, has been shown to be significantly elevated in individuals with chronic SCI compared with non-injured controls.^12^ This is of clinical relevance given that cfPWV has been directly linked with cardiovascular mortality in non-injured individuals.^13^

Reduced mobility as a result of both injury-related functional impairments and the need for medical stabilisation post-SCI can cause the cardiovascular system to undergo immediate alterations in its function as it adjusts to the new reduced metabolic demands.^14^ In as little as 6 weeks after injury, peripheral arteries in the paralysed lower limbs can undergo remodelling, resulting in reduced flow and diameter of the femoral artery.^15^ This remodelling is in conjunction with the diminished sympathetic tonic activity to the blood vessels below the lesion,^16^ which can result in profound hypotension. Moreover, individuals with higher-level injuries (ie, cervical and upper-thoracic injuries above the sixth thoracic level (≥T6)), often experience more pronounced hypotension due to potentially disrupted autonomic pathways.^17 18^ Beyond the acute pathological issues associated with blood pressure (BP) variability,^19^ chronic exposure to unstable BP has been shown to detrimentally impact cardiac and vascular structure and function,^6 20^ which can be measured via ultrasound. Assessing the autonomic regulation of the cardiovascular system non-invasively can be achieved using heart rate variability (HRV).^21^ Specifically, the frequency domain of HRV predicts cardiovascular dysfunction in individuals with SCI.^22^

SCI significantly contributes to obesity by altering fat-free mass and causing physical impairments such as paralysis or paresis, which restricts energy expenditure associated with movement, thereby increasing cardiometabolic risk.^23^ Such changes disrupt metabolic homeostasis,^24 25^ resulting in disorders such as insulin resistance and dyslipidaemia, which in turn increases the risk of developing type 2 diabetes mellitus and CVD in individuals with SCI.^26^ Individuals with both traumatic and non-traumatic SCI experience an elevated risk of CVD, highlighting the importance of routine CVD risk screening during rehabilitation for both groups.^27^

Reduced physical activity levels due to SCI-related immobility, coupled with decreased fitness and sympathetic nervous system dysfunction in individuals with injuries ≥T6, further limits the capacity to achieve higher energy expenditures through exercise.^28^ A Canadian-based study showed that individuals with SCI undergoing inpatient rehabilitation experience minimal cardiovascular stress, spending a median of only 5 mins/day performing activities at ≥40% heart rate reserve. This level of activity is not sufficient to obtain a cardiovascular training effect to optimise cardiovascular health, despite the participants self-reporting that they were doing a sufficient volume of exercise.^29^ Therefore, accurately assessing physical activity levels during the subacute period of SCI is also crucial for clinicians to tailor interventions to mitigate the aforementioned CVD risks in individuals living with SCI. However, accurately measuring physical activity levels in individuals with SCI is challenging due to the altered movement patterns and variations in metabolically active muscle mass.^30^ These challenges may be overcome by using an individually calibrated and validated multisensor device (as proposed in this trial) to provide valuable insight into the amount of physical activity achieved during inpatient SCI rehabilitation in the UK.^31^

Individuals with SCI often report a lower health-related quality of life (HRQOL) compared with non-injured individuals.^32^ Various factors influencing HRQOL following SCI include pain,^33 34^ fatigue^35^ and both cognitive^36^ and motor^37^ impairments. Common types of pain include musculoskeletal and neuropathic pain.^34^ Musculoskeletal pain, which can occur due to muscle spasm or the overuse of the arms and shoulders,^38^ can hinder independence and lead to reduced aerobic performance during activities of daily living and chronic postural deviations.^39^ Neuropathic pain is considered the most debilitating pain that is spontaneous in the majority of individuals with SCI and can manifest as increased pain with both noxious and innocuous stimulation.^40^ Pain is prevalent in 60%–80% of individuals with SCI, with one-third reporting severe pain.^40^ Chronic fatigue affects around 56% of individuals with SCI, which is almost double the rate observed in the non-injured population.^41^ Multiple factors contribute to cognitive impairments in individuals with SCI,^42^ including medications (eg, opioids such as pregabalin and gabapentin),^43 44^ traumatic brain injury, which occurs in almost 60% of individuals with high-level injury,^45^ and autonomic cardiovascular dysfunctions.^19 46^ Memory and learning impairments can be a challenge for the required development of new skills during rehabilitation.^47 48^ Therefore, enhancing HRQOL necessitates evaluating cognitive abilities, developing targeted rehabilitation strategies to mitigate pain and fatigue, while also improving motor function and ensuring that a substantial time period is devoted to promoting targeted physical activity outside of standard of care physical therapy.^49^,^52^

### Exercise interventions to improve cardiovascular health in individuals with subacute SCI

The cardiovascular stress during inpatient rehabilitation in the UK remains to be objectively quantified, as we have done previously to capture habitual free-living behaviours in community-dwelling individuals with SCI.^31^ Preclinical evidence indicates that early administration of exercise following experimental SCI leads to more pronounced cardiohaemodynamic benefits than delayed exercise administration.^53^ This is likely important in the clinical setting as literature indicates that individuals with SCI exhibit significant reductions in cardiac function within the first 6 months following injury.^54 55^ Arm-crank exercise training (ACET) is an inexpensive and widely used exercise modality for individuals with SCI^56^ that has been shown to improve cardiorespiratory fitness.^57^ Despite the amount of evidence supporting the benefits of ACET for cardiovascular health in chronic (>12 months) SCI,^57^,^59^ there is little understanding of whether the same effect can be expected in subacute SCI and whether an exercise intervention initiated in this stage postinjury mitigates declines in cardiac structure and function.^60^ A recent systematic review indicated very low levels of evidence for the benefits of exercise in the subacute phase following SCI,^58^ primarily due to the limited and poorly designed research studies available.

Given the known benefits of ACET for individuals with chronic SCI, this study aims to investigate the effects of exercise on cardiovascular health parameters in patients with subacute SCI. It is also essential to qualitatively assess the feasibility and implementation of ACET in the subacute rehabilitation setting. Understanding both patient and healthcare provider/staff perspectives on receiving and delivering an ACET intervention, respectively, is crucial for the development of effective rehabilitation tailored to individuals with SCI. While regular physical activity has been reported to have significant health benefits for individuals with SCI,^61^ it is equally as important to consider the potential overburdening of inpatients alongside their standard of care, as well as both the clinical and cost-effectiveness of promoting additional prescribed aerobic upper-body exercise in the rehabilitation pathway.^62^

### Trial objectives

We aim to determine whether the addition of ACET to standard of care treatment during inpatient rehabilitation within the subacute period following SCI has beneficial effects over the current standard of care (control group, CON) rehabilitation on arterial stiffness (measured via cfPWV) and secondary health outcomes: (1) blood biomarkers related to CVD, (2) cardiac structure and function, (3) extracranial vasculature, (4) HRQOL, (5) cognitive function, (6) physical activity level, (7) cardiorespiratory fitness, (8) motor function and (9) feasibility outcomes in individuals with subacute SCI. In comparison to CON, we hypothesise that the physical and metabolic stimuli of ACET will maintain cfPWV at a level that is comparable to normative age-matched values reported in the general population.^63^

## Methods and analysis

### Study design and setting

This is a single-centre, two parallel-group, randomised controlled trial of a 10-week ACET exercise intervention compared with standard of care inpatient rehabilitation with a 6-month follow-up assessment after discharge for HRQOL outcomes. This protocol is approved by the Integrated Research Application System (IRAS; 315098) and the design of the study is aligned with the consensus-based recommendations for designing, delivering, evaluating and reporting exercise-intervention research involving people with SCI.^64^ The Standard Protocol Items: Recommendations for Interventional Trials^65^ checklist can be found in the online supplemental material (Research Checklist). Participant eligibility to enter the study is within 12 months post-SCI to reflect a realistic representation of the SCI population undergoing rehabilitation in the UK. The site initiation visit was completed on 7 September 2023, with the first participant assessment in November 2023. Participant recruitment will stop in September 2025. The study will be conducted in accordance with ethical principles for studies involving human participants set out in the Declaration of Helsinki.

The study and all recruitment will be conducted at the Robert Jones and Agnes Hunt (RJAH) Orthopaedic Hospital. This SCI Rehabilitation Centre caters to a wide catchment area, serving a population of 10 million people that includes the West Midlands (where the University of Birmingham is situated). The Midland Centre for Spinal Injuries (MCSI) at RJAH offers a multidisciplinary approach to SCI treatment that focuses on maximising neurological recovery while minimising complications, ensuring a holistic approach to patient care. This includes a commitment to innovation to transform care, which aligns well with the objectives of the study to evaluate the efficacy of an ACET intervention.

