### Recruitment and consent process

Participants will be identified by trained clinical staff on admission to the rehabilitation hospital, based on the eligibility criteria outlined in table 1. If patients express an interest in the study, a participant information sheet will be given to them along with the contact information of the research team should they have any questions. Interested and eligible participants will be approached by a study team member and asked to provide written informed consent (>24 hours after receiving the participant information sheet and receiving a full verbal explanation of the study). If participants are unable to provide a signature due to their injury, a witness will be present to sign confirming the prospective participant’s verbal consent.

**Table 1 T1:** Participant inclusion and exclusion criteria

Inclusion criteria	Exclusion criteria

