For patients: At least 18 years old Males and females Have had an SCI* (AIS A, B, C or D) between C5 and T12 levels within 12 months; injuries graded AIS D on consent must be using a wheelchair >75% of the time for mobility Are cleared by their medical team to begin standard of care rehabilitation. Can move their shoulders and arms voluntarily to operate the arm-crank ergometer. Compliance: understands and is willing, able and likely to comply with all study procedures and restrictions. Consent demonstrates an understanding of the study and willingness to participate, as evidenced by voluntary written informed consent. For healthcare providers/staff: Currently be a member of the medical team supporting subacute spinal cord injured patients at MCSI. Be at least 18 years old. Be involved in the clinical care/rehabilitation of patients (eg, clinician, occupational therapist or physical therapist)	Pregnant (women who become pregnant will be advised to notify clinical staff, and on notification, will be withdrawn from the trial) Under the age of 18 years. Have an SCI lower than the T12 neurological level. Have an SCI above the C5 neurological level, intubation, a tracheostomy in situ or requires mechanical ventilation. Medical complications or premorbidities from the injury that, in the opinion of the healthcare or research team, would restrict or prevent the participation in exercise rehabilitation, pose undue personal risk or introduce bias into the trial. Co-occurring traumatic brain injury or cognitive impairment that either impacts the ability to follow study instructions and/or provide informed consent. Unable to provide fully informed consent.

* Spinal Cord Injury Levels & Classification.

AIS, American Spinal Injury Association (ASIA) Impairment Scale; C, cervical; MCSI, Midland Centre for Spinal Injuries; SCI, spinal cord injury; T, thoracic.

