Autonomic Dysfunction in Spinal Cord Injury	X						X	
Primary Outcome								
Carotid-Femoral Pulse Wave Velocity		X		X			X	
Secondary outcomes								
Blood sampling		X		X			X	
Health-Related Quality of Life Standard Questionnaires		X		X			X	X
Digit Span and Symbol Digit Modalities Test		X		X			X	
Wheelchair Users Shoulder Pain Index		X		X	X(weekly)		X	X
Cardiovascular Ultrasound		X		X			X	
Resting heart rate variability		X		X			X	
24-hour ambulatory blood pressure monitoring			X			X		
Rehabilitation energy expenditure (>3 days of monitoring) and free-living heart rate variability			X			X		
Motor function testing			X				X	
Arm cycle exercise familiarisation			X					
Cardiorespiratory fitness and heart rate recovery				X			X	
Continuous exercise heart rate and episodic (pre/post) Blood pressure monitoring					X(all sessions)			
Feasibility and Acceptability Questionnaire							X	
One-to-one Interview							X	

* For the A4 time point, only Health -Related Quality of Life Questionnaires and WUSPI will be completed.

Cardiorespiratory fitness assessments commence at A2 following a 20 min familiarisation session on the arm-crank ergometer, which will be performed by all participants between A1 and A2 (see table 2). The duration between A1 and A2 will be at least 2 weeks, although this timeframe is flexible based on the clinical needs of the patient. For example, prolonged bed rest may necessitate a longer interval before initiating standard of care rehabilitation due to factors such as fatigue or secondary complications such as pressure sores or urinary tract infections. At A4, occurring 6 months after A3 (ie, postintervention), we will remotely reassess HRQOL outcomes to determine whether there are differences between the ACET and CON groups.

A1, A2 and A3 assessments will be carried out within MCSI at the RJAH. A4 follow-up assessments will be conducted virtually. To ensure fidelity of assessments, the CI and research personnel held initial meetings for standardised training and logistics. Regular executive committee meetings consisting of the CI ([name]), site PI ([name]), site clinical lead ([name]), postdoctoral research fellow ([name]), research nurse, healthcare assistant and other MCSI staff will convene to discuss any data collection issues or safety issues that arise.

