#### Left ventricular structure and function

Cardiac structure and function has been shown to rapidly decline between 3 and 6 months during the subacute period of SCI.^54 55^ Furthermore, alterations to cardiac function and mechanics have been reported in individuals with chronic SCI following an exercise intervention.^84 85^ To measure cardiac indices, transthoracic echocardiography will be performed using a Vivid *iq* ultrasound system (General Electric Healthcare, Buckinghamshire, UK) in accordance with recommendations of the American Society for Echocardiography and European Association of Echocardiography.^86^ Images will be stored for offline analysis using specialised computer software (EchoPAC, General Electric Healthcare, Buckinghamshire, UK) by a single analyser. The average of three cardiac cycles will be used to determine left ventricular (LV) structural and functional indices. Indices of LV mechanics will be analysed using two-dimensional speckle-tracking software in accordance with recommended guidelines.^87^

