### Statistical analysis

The Shapiro-Wilk test will be used to test the distribution of the continuous variables for demographic and outcome measures. Continuous variables will be reported as mean±SD for normally distributed data or median with IQRs for non-normally distributed data; categorical variables will be reported as frequency. Specific injury characteristics will be considered for subanalysis (ie, injury level, injury severity). A two-way repeated measures analysis of variance (ANOVA) will be applied to examine the main effects of the group/time and group–time interaction. Post hoc analyses will be conducted where significant group-time interaction effects are identified. Significance level will be set at 0.05 for all statistical tests. Standardised effect sizes (Cohen *d*) will also be calculated and interpreted based on the following criteria: small (*d*=0.2), medium (*d*=0.5) and large (*d*=0.8) effects.^128^

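### The 12-month limit is checked only at study entry, so training can start after the subacute period has ended, and time since injury has no place in the stated analysis

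*Protocol article*

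**What the plan says.** **The period of interest.** The abstract defines subacute as less than 12 months after injury. The Background subsection on exercise interventions calls injuries older than 12 months chronic. Trial objectives places the addition of ACET "during inpatient rehabilitation within the subacute period following SCI". The Discussion describes early exercise as exercise begun within 12 months.

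**Where the limit is applied.** Study design and setting states: "Participant eligibility to enter the study is within 12 months post-SCI to reflect a realistic representation of the SCI population". Table 1 repeats it as an inclusion criterion, with an injury "between C5 and T12 levels within 12 months". On timing of entry, Recruitment and consent process says: "Participants will be identified by trained clinical staff on admission to the rehabilitation hospital".

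**What comes between entry and training.** Under Randomisation, allocation follows both the A1 and A2 assessments. Under Assessments, after Table 2: "The duration between A1 and A2 will be at least 2 weeks, although this timeframe is flexible". The same paragraph explains that "prolonged bed rest may necessitate a longer interval before initiating standard of care rehabilitation". No maximum is given, and no step at A2 looks again at time since injury.

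**Why timing matters to this trial.** The Background cites preclinical evidence favouring early over delayed exercise and places loss of cardiac function in the first 6 months. Left ventricular structure and function says: "Cardiac structure and function has been shown to rapidly decline between 3 and 6 months during the subacute period of SCI".

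**The analysis.** Statistical analysis names a two-way repeated measures ANOVA with group, time and their interaction, and no covariate. On subgroups: "Specific injury characteristics will be considered for subanalysis (ie, injury level, injury severity". Randomisation is in blocks to balance group sizes, and no stratification is described.

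**The concern.** There are two linked problems.

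First, the limit and the question refer to different moments. The question concerns exercise started within 12 months of injury, while the limit governs consent and entry. Because the lead-in is open-ended, an eligible participant can be randomised and begin training after month 12. The reasons given for a longer lead-in are bed rest and complications, so any delay falls mainly on the more complicated cases. The trial would then include people whom its own definitions place in the chronic phase, while its conclusions would be worded for the subacute phase.

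Second, the case for the trial depends on how long after injury exercise starts. If cardiac function changes quickly in the early months, people randomised at different times after injury will differ in their natural 10-week change. That difference adds spread to the cardiac outcomes, and with 42 participants it can also fall unevenly between the arms by chance. The date of injury is needed to judge eligibility and could absorb part of that spread, but the stated analysis does not use it.

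**Working it through.** The plan gives no figure for this point, so there is none to reproduce. The check is calendar arithmetic followed by a comparison of sections.

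**Step 1. When training can start.** Inputs: entry limit of 12 months (Study design and setting; Table 1); lead-in L from A1 to A2 of at least 2 weeks (Assessments); randomisation after A2 (Randomisation). Twelve months is 365.25/7 = 52.18 weeks. The 2-week lead-in is the protocol's minimum. The 4-week and 8-week values are assumptions, used to show the range because no maximum is stated.

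- Start of training for someone entering at the limit: 12 × (52.18 + L)/52.18 months.
- Latest entry that still allows a start by month 12: 12 × (52.18 − L)/52.18 months.
- Part of the entry window from which training starts after month 12: L/52.18.

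| Lead-in L | Start if entry is at 12 months | Latest entry for a start by month 12 | Part of the window affected |
|---|---|---|---|
| 2 weeks (minimum) | 12.5 months | 11.5 months | 3.8% |
| 4 weeks (assumed) | 12.9 months | 11.1 months | 7.7% |
| 8 weeks (assumed) | 13.8 months | 10.2 months | 15.3% |

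In whole weeks, with the minimum lead-in: 52 − 2 = 50, so entry after week 50 leads to a start after month 12, and 2/52 is about 4% of the window. These are shares of the calendar window, not of participants. They would equal shares of participants only if entry were spread evenly over 12 months, which the documents do not suggest.

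**Step 2. Rationale against analysis.** The Background and the left ventricular section tie cardiac change to the first 6 months, or to months 3 to 6. The abstract states it more broadly, as reductions within the first year. On any of these readings, time since injury is a plausible predictor of cardiac change over 10 weeks. Statistical analysis has only group, time and their interaction. Its time factor is the assessment occasion, not time since injury. The subanalysis list is closed by its wording and contains level and severity only.

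**Step 3. The primary outcome.** For carotid-femoral pulse wave velocity (cfPWV), the Background says only that it is raised in chronic injury. No section gives its course over the months after injury, so the documents do not show how far time since injury would explain 10-week change in cfPWV.

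**The case against.** The strongest reply has four parts.

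*The wide window is deliberate.* The protocol wants a realistic picture of the UK rehabilitation population. This stands as a reason for admitting people up to 12 months. It does not explain why the limit ignores the lead-in.

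*Late entrants will be few.* Patients are identified on admission, the standard-of-care section describes transfer from trauma centres after a new injury, and the Discussion speaks of newly injured people. This largely stands and keeps the point small. It also rules out assuming entry spread evenly over 12 months in order to claim that a large fraction start after the cardiac decline.

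*Only initiation matters.* A reader might infer that anyone whose 10 weeks of training run past month 12 is outside the question. The objective read alone could allow that, but the Background and Discussion both speak of starting exercise in the subacute stage. Finishing later contradicts neither, and requiring all 10 weeks inside the window would work against the stated aim of representativeness.

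*Covariates belong to the statistical analysis plan, and allocation is randomised.* Both statements are fair. A plan not shown may name the covariate, and randomisation prevents systematic bias; the Randomisation section itself attributes any imbalance to chance. The covariate is therefore a recommendation for pre-specification, made because the article lists its subanalysis factors and omits the one its rationale relies on.

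**Conclusion.** The point holds in a limited form. The entry-only limit does not match the objective and Discussion. With the minimum lead-in the mismatch covers entry after about week 50, roughly 4% of the window, and more if the lead-in is longer. The share of participants affected is probably small and cannot be calculated, because the documents give neither a distribution of time since injury nor a maximum lead-in.

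Leaving time since injury out of the stated analysis forgoes an inexpensive gain in precision for the cardiac outcomes. For cfPWV the gain is uncertain.

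A reader might go further and infer that late starters dilute the primary comparison, or that a null or positive result could not be interpreted. The documents do not support this. The timed decline is cardiac, hence a matter of secondary outcomes; the abstract also places it within the first year; no time course is given for cfPWV; and the Background reports benefit of ACET in chronic injury, so late starters cannot be assumed to gain nothing.

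**What to change.** 1. Reconcile the sections. Either check the 12-month limit at A2, when participants are randomised, or keep the entry rule and describe the population throughout as people who entered within 12 months of injury. If recruitment has closed (the protocol gives September 2025), the second option remains open.

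2. Pre-specify time from injury to A2 as one continuous baseline covariate: chiefly for the cardiac structure and function outcomes, and as a supporting analysis for cfPWV. It must bear on the change from A2 to A3, either as a predictor of that change or through its interaction with assessment time. As a main effect alone in the repeated measures model it would not adjust the group-by-time comparison. Fix this before the blinded analysts begin.

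3. Report any interaction of group with continuous time since injury as exploratory only. With 42 participants, a split at 6 months would average about 10 per cell (42/4 = 10.5) before dropout.

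4. Report the distribution of time from injury to A2 by arm, and the number who started training after month 12.

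Cost: one degree of freedom in the analysis of change, no new data collection because the injury date is needed for eligibility, and, if the limit is checked at A2, possibly a few late entrants excluded.
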